## Abstract

**Introduction:**

The workforce shortage in the healthcare context is a growing issue that exerts detrimental effects on employees (e.g., higher workload) and patients (e.g., suboptimal patient care). Since traditional approaches alone may not be enough to solve this problem, there is a need for complementary innovative digital health solutions, such as socially assistive robots. Hence, the proposed study aims to investigate the effects of gamified nursing education and physiotherapy delivered by a socially assistive robot on patient- (engagement, perceived quality of care) and employee-related outcomes (perceived self-efficacy, workload).

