As socially assistive robots can provide education without the usual restraints imposed upon human employees (e.g., the robot can effortlessly repeat the same instructions multiple times) and in a gamified manner that may facilitate motivation and learning, we expect positive effects of interactive digital assistance on patient-related outcomes. More specifically, we hypothesize that patients will exhibit higher levels of patient engagement (H1) and perceived quality of medical care (H2) after being subjected to standard care with additional gamified nursing education and general/respiratory physiotherapy (delivered by a socially assistive robot) compared to levels at the beginning of the study. Furthermore, we hypothesize that patients exposed to standard care with additional gamified nursing education and general/respiratory physiotherapy (delivered by a socially assistive robot) will experience larger improvement of patient engagement (H3) and perceived quality of medical care (H4) compared to patients exposed solely to standard care (human interaction only). Additionally, due to socially assistive robots’ potential to be involved in patient care and help with some of the work tasks, we hypothesize that employees will exhibit higher self-efficacy (H5) and experience lower workload (H6) during time periods when a socially assistive robot is deployed compared to time periods when a socially assistive robot is not deployed.

In addition to our primary hypotheses, we aim to determine the percentage of non-urgent communication taken up by the social robot (RQ1), the amount of employees’ time saved by such robot-human interactions (RQ2), and the extra time of interaction provided to patients by using a socially assistive robot (RQ3). We are also interested in how these variables (e.g., the number/percentage of AI interactions) correlate with both patient- and staff-related outcomes (RQ4). Lastly, we are also interested in patients’ user experience concerning the use of a socially assistive robot (RQ5). Answering these research questions and testing the hypotheses stated above will generate a novel and comprehensive insight into the effectiveness of using socially assistive robots in healthcare.

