## Methods and analysis

### Socially assistive robot Pepper

The Pepper robot, developed by SoftBank Robotics, is a 120 cm tall social humanoid robot optimized for human interaction and engaging with people through conversation and a touch screen. It is capable of natural movement, navigation, speech recognition, and dialogue, and is equipped with perception modules and various sensors for multimodal interactions (e.g., microphones, infrared sensors, cameras, and sonars). These functions allow for smooth interaction that does not require any specific training. The Pepper robot also has several safety mechanisms, such as bumper sensors, that prevent it from physically harming participants (29). For the purposes of the proposed study (and other studies within the H2020 project HosmartAI), the robot was taught to understand and express gestures, facial expressions, and speech in the Slovenian cultural context and language. It was also taught to perform exercises and scenarios that are part of the intervention (see section “Study design”).

The robot was first extensively tested in a laboratory setting. After this stage, we introduced the robot to employees in both participating departments. The robot was then extensively pilot tested on-site over the period of 3 months, with significant input from the clinical staff.

Despite extensive pilot testing, Pepper will be constantly supervised throughout the study by at least one researcher, enabling us to detect failures immediately and make quick repairs if needed. In the case of more severe malfunctions, the robot will be temporarily replaced with a backup unit. Moreover, in the rare event of the second unit also malfunctioning, the study will be temporarily put on hold and participants from the interrupted iteration will be excluded from analyses. The study will continue when at least one robot is working properly again.

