### Study design

The proposed study employs a between-within interaction design with multiple iterations. Patients and employees participating in the study will be recruited in a University Clinical Centre Maribor, Slovenia. The study will be carried out in 1-week intervals, followed by a 1-week washout period between each iteration. Overall, the study will be conducted over 2 years or less if the desired sample size is reached sooner.

Patients admitted to vascular and thoracic surgery wards for an elective (non-emergency) procedure will be screened for eligibility regarding the inclusion and exclusion criteria. Eligible participants will then be informed about the study characteristics and asked to fill out an informed consent form. Those who will consent to participate in the study will participate for 3–5 days. Depending on the week (see Figure 1), participants will be allocated to the standard care group (i.e., a control group that will not interact with a socially assistive robot) or standard care group with additional robot interactions. Participants from both groups will first be informed about the study and fill out the baseline questionnaires (demographic data, engagement, and perceived quality of care). Similarly, participants from both groups will be subjected to standard nursing education and general/respiratory physiotherapy delivered by nursing and physiotherapy staff. However, the patients allocated to the standard care group with additional robot interactions will additionally be subjected to nursing education and general/respiratory physiotherapy delivered by a socially assistive robot. Moreover, they will be able to call the robot for additional assistance (not related to nursing education and physiotherapy) during the whole study period. At the end of their participation, patients from both groups will be asked to fill out the questionnaires (engagement, perceived quality of care) for the second time. Patients from both groups will also be asked to rate the education and physiotherapy they received during the study period. Moreover, patients that will interact with a socially assistive robot, will also fill out the User Experience Questionnaire (30) at the end their participation.

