## Discussion

Despite the growing need for automated support and the constantly improving social robots, now capable of providing versatile services—such as education, social interaction, and entertainment—in a user-friendly manner, their large-scale implementation is progressing rather slowly (14, 17). This is disconcerting, as the existing studies suggest that their use is positively associated with the desired patient outcomes and can alleviate the workload of hospital staff (20–22, 24, 25). One of the plausible reasons for this gap is a relatively low number of systematic studies conducted in real-life settings, employing adequate sample sizes and investigating the effects on various outcomes. As put by Kvedar (42) when referring to digital health in general: “*One critical piece moving us along the curve is the accumulation of high-quality evidence, and there is no better way to curate evidence than through investigative inquiry*” (para. 6).

Our study is hence designed to extend evidence on gamified digital approaches and socially assistive robots in the context of healthcare. More specifically, this study’s main strength is that it will provide crucial data on the effects of gamified nursing education and general/respiratory physiotherapy delivered by a socially assistive robot on patients as well as staff. As such, it will provide some answers regarding the practical value of deploying social robots and their potential for facilitating engagement and perceived quality of care among patients. At the same time, it seeks to investigate whether social robots, as complementary devices to standard care, can reduce employees’ workload. To ensure a high enough quality of evidence provided by our study, we will conduct a rigorous study and use validated questionnaires to measure a wide variety of patient- and staff-related outcomes. Additionally, we will obtain a large enough sample of patients and employees. Throughout the process, we will follow the relevant recommendations and guidelines and pay attention to ethical considerations.

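### The aim, H3/H4 and the Discussion credit the arm difference to robot-delivered education and physiotherapy, but the trial tests a robot package that also includes unrelated on-call assistance

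*Protocol article*

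**What the plan says.** **The effect claimed.** The protocol article's abstract sets out to "investigate the effects of gamified nursing education and physiotherapy delivered by a socially assistive robot on patient- (engagement, perceived quality of care") and employee outcomes. In the Introduction, H3 and H4 state that "patients exposed to standard care with additional gamified nursing education and general/respiratory physiotherapy (delivered by a socially assistive robot) will experience larger improvement" in engagement and perceived quality of care, "compared to patients exposed solely to standard care (human interaction only"). The Discussion gives as the study's main strength that "it will provide crucial data on the effects of gamified nursing education and general/respiratory physiotherapy delivered by a socially assistive robot".

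**What the arms receive.** Under Study design, both arms get staff-delivered education and physiotherapy. Robot-arm patients "will additionally be subjected to nursing education and general/respiratory physiotherapy delivered by a socially assistive robot". The next sentence adds a second component: "Moreover, they will be able to call the robot for additional assistance (not related to nursing education and physiotherapy) during the whole study period". The comparator is "a control group that will not interact with a socially assistive robot". The Measures section likewise describes the choice between a human and an AI call device only for robot iterations.

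**Supervision.** The section on the robot says that "Pepper will be constantly supervised throughout the study by at least one researcher", so that failures are detected at once and repaired quickly.

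**Analysis.** Each patient outcome is tested in a mixed ANOVA with group (two levels) and time (T1, T2). Calls, interactions and encounter times are recorded. They feed research questions that are answered descriptively or with Pearson correlations.

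**The concern.** H3 and H4 name one added component, while the robot arm has at least two. The protocol itself labels the second as unrelated to the first, so it cannot be read as part of the hypothesised exposure.

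The second component could plausibly move the outcomes. Perceived quality of care is a global self-rating of the care received, and patients know whether they had a robot to call. The Introduction lists patient education and non-critical communication as separate tasks that suffer under high workload. RQ3 expects the robot to give patients extra interaction time.

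At stake is what a positive result may be said to show. A significant group-by-time term would, under the present wording, be reported as support for gamified robot-delivered education and physiotherapy, although on-call assistance could have produced part or all of it.

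**Working it through.** **1. Components against hypothesis**

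| Component | Robot arm | Control arm | Named in H3/H4 |
|---|---|---|---|
| Staff education and physiotherapy | yes | yes | yes, as standard care |
| Robot education and physiotherapy | yes | no | yes |
| On-call robot assistance on other matters | yes | no | no |
| Researcher supervising the robot | stated for the robot; patient contact not stated | contact or its absence not stated | no |

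The third row is explicit and carries the point alone. The fourth is only a possibility.

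**2. Can the analysis separate the rows?** With group as the only between-subjects factor, rows two and three are present together in one arm and absent together in the other. The interaction estimates their joint effect. The recorded calls and encounter times do not change this: patients decide how much on-call help to use after allocation, so a correlation between use and outcome gives no causal share. The Measures section also states no split of encounter time between education/physiotherapy and on-call help.

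**3. The plan's own sample size.** Inputs from Participants and recruitment: f = 0.15, α = 0.05, power 0.80, k = 2 groups, m = 2 measurements. The T1-T2 correlation ρ is not given; 0.5 is assumed.

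- Noncentrality: λ = f²·N·m/(1 − ρ) = 0.0225 × 90 × 2/0.5 = 8.1, on 1 and 88 degrees of freedom.
- Power = 0.804, so the stated figure of about 90 is reproduced.
- The N needed for other values of ρ is 178 (0), 126 (0.3), 56 (0.7) and 38 (0.8).

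In a 2 × 2 layout the between-arm difference in change, D, in SD units, is 4f = 4 × 0.15 = 0.60. Check with 45 per arm and SD of change √(2(1 − 0.5)) = 1: (0.60/√(2/45))² = 8.1, the same λ.

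**4. Illustration of misattribution.** Suppose robot education and physiotherapy have no effect and on-call assistance shifts the score by D. The values of D are assumed; the documents give none. With f = D/4 and N = 90:

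| D (SD) | λ at ρ = 0.5 | P(significant), ρ = 0.5 | ρ = 0 | ρ = 0.8 |
|---|---|---|---|---|
| 0.10 | 0.225 | 0.076 | 0.063 | 0.115 |
| 0.20 | 0.900 | 0.155 | 0.102 | 0.317 |
| 0.30 | 2.025 | 0.291 | 0.169 | 0.605 |

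An on-call contribution of 0.20 SD would be 0.20/0.60, one third of the effect the trial is sized for.

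These probabilities look like inflated error only if the narrow effect is the target. For the package effect they are ordinary power.

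**The case against.** The strongest reply is that this is a package trial and says so. The last paragraph of the Introduction's background gives the aim as the effects of the robot itself, partly operated and supervised by humans. The sentence leading into the hypotheses speaks of interactive digital assistance. The arm is labelled throughout as standard care with robot interactions, and the Discussion also mentions the practical value of deploying such robots. Comparing an add-on service with standard care is a legitimate design. The plan also logs calls and encounters and relates them to outcomes under RQ1 to RQ4.

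Much of this stands. The test is valid for the robot-level aim, and neither design nor analysis needs to change. It does not remove the mismatch, because the abstract, H3/H4 and the stated main strength claim a narrower effect than the arms can deliver. Nor does it help that a statistical analysis plan may exist: the fault is not an omission but two statements in the article that do not match.

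Two stronger readings are tempting and are not supported.

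- *A researcher is constantly with robot-arm patients and absent from controls.* The article states supervision of the robot, not bedside contact. It says that patients are observed for distress throughout the study, without naming the observer or limiting this to one arm. Differential researcher attention is possible but not documented.
- *The false-positive rate is 8% to 29%.* Those figures rest on assumed on-call effects. On-call use may also partly replace staff contact, as RQ1 and RQ2 suggest, so it need not be purely extra attention.

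**Conclusion.** The point holds as a mismatch between the claimed effect and the tested contrast. The group-by-time test addresses standard care against standard care plus the whole robot package. It does not isolate robot-delivered gamified education and physiotherapy, and no planned analysis does. A positive H3 or H4, as worded, would be credited to an exposure that the control does not isolate. The limitations paragraph does not mention this.

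The conclusion rests only on the explicit on-call sentence, the control description and the two-level group factor. It needs no assumed effect size and no assumption about researcher contact, and the sample size is unaffected. The matter should be corrected before results are reported, because it determines what the trial may conclude.

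**What to change.** 1. Reword the abstract's aim, H3/H4 and the Discussion claim to the contrast the trial has: standard care versus standard care plus a supervised robot package of additional education/physiotherapy and on-call robot assistance.
2. State that no effect will be attributed to gamification, or to robot-delivered education and physiotherapy as such.
3. Add the bundling to the limitations. Mention contact with the supervising researcher there only as a possible further difference between arms.
4. Add encounter type (education/physiotherapy or on-call) to the log described under Measures. Report it descriptively only, because on-call use is chosen by patients after allocation and cannot apportion the effect.

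The cost is a few sentences and one field in an existing log. There are no extra patients, no new arm and no change to care. The downside is a narrower claim.

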**FIGURE 1 F1:**
[figure not shown]
Study design: patients.

The study will be conducted in several 1-week iterations with a washout period between them (to provide enough time for new patients to be admitted). Specifically, patients will receive standard care in week 1, followed by a washout period in week 2. Patients in week 3 will then receive standard care together with robot interactions, followed by a washout period in week 4. In week 5, patients will again receive standard care. The study procedure (for patients) is outlined in Figure 1. It is worth noting that all additional variables (e.g., number of interactions with a robot) will be collected continuously during each relevant iteration. Additionally, the instructions of all self-report questionnaires will be adapted to reflect the chosen time periods and tasks. Throughout the study, patients will be observed for signs of high distress and excluded from the study if needed.

In terms of intervention content, the nursing education will contain critical information on wound care, home care considerations, and daily care explanations. On the other hand, general and respiratory physiotherapy will consist of selected instructions and exercises that can be delivered both by a human and a robot. The AI-delivered nursing education and physiotherapy instructions will employ elements of gamification.

Similarly to patients, nursing and physiotherapy staff working on vascular and thoracic surgery wards will first be screened for eligibility regarding the inclusion and exclusion criteria. Eligible participants will then receive a brief description of the study and an informed consent form. Those who will consent to participate in the study will fill out the questionnaires twice, over a 3-week period. They will first fill out the questionnaires after a week of standard care (end of week 1: baseline self-efficacy and workload) and then again at the end of the first iteration of using a socially assistive robot (end of week 3: self-efficacy and workload after the intervention). To increase the robustness of results, the same protocol will be carried out thrice during the course of the study; at the initial deployment of a robot, after 1 year (T3 and T4), and right before the end of the study (T5 and T6). This will also enable us to investigate whether the difference between self-efficacy/workload at the time of robot use and non-use changes over time (once employees become more accustomed to the robot). The study procedure (for employees) is outlined in Figure 2. Again, the instructions of all self-report questionnaires will be adapted to relevant time periods and tasks.

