The proposed study is not without limitations. First, while our study will offer important insight into the effectiveness of interactive digital assistance, a randomized controlled trial with a larger sample size may be needed to further determine the effects of such intervention. Second, even though all surgery patients conforming with the inclusion criteria will be invited to participate in the study, it is plausible that only patients with more favorable attitudes toward technology will agree to participate in the study. This might lead to a sample that is generally younger and more educated (43, 44), possibly biasing the results on the effectiveness of social robot-delivered education and physiotherapy. Third, due to the specific characteristics of vascular and thoracic surgery patients (e.g., length of hospitalization), their exposure to the social robot will be somewhat short. Hence, the study will primarily focus on initial reactions to the socially assistive robot, whereas the trajectories of what happens over a more extended period (i.e., continued use), which can differ from initial reactions (45), will have to be explored in future studies. Lastly, in the present study, the social robot will be limited to a few specific services, physical locations, and one hospital, making it difficult to provide general and final conclusions on the effectiveness of social robots in hospitals.

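### Study weeks run in a fixed standard/robot order, so the arm is predictable at booking and already set at consent; consent could differ by arm and bias H3/H4

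*Protocol article*

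**What the plan says.** The protocol article, under Study design, assigns patients by calendar: "Depending on the week (see Figure 1), participants will be allocated to the standard care group", or else to standard care with added robot interactions. The text after Figure 1 fixes the order. It begins "patients will receive standard care in week 1, followed by a washout period in week 2". It continues "Patients in week 3 will then receive standard care together with robot interactions, followed by a washout period in week 4", and then "In week 5, patients will again receive standard care". No random order and no concealment of the order is described.

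The population is "Patients admitted to vascular and thoracic surgery wards for an elective (non-emergency) procedure". After screening, "Eligible participants will then be informed about the study characteristics and asked to fill out an informed consent form". Baseline engagement and perceived quality of care are then collected in both groups.

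The Discussion says that every surgery patient who meets the inclusion criteria will be invited, but that "it is plausible that only patients with more favorable attitudes toward technology will agree to participate in the study". It presents this as a feature of the whole sample. It also concedes that a larger randomised trial may be needed.

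H3 and H4 are tested with a group-by-time mixed ANOVA for each outcome (Analyses of patient-related outcomes). Staff complete questionnaires after a standard week and then after a robot week, and this sequence is run three times: at first deployment, at one year and just before the end.

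**The concern.** H3 and H4 compare improvement between patients who stayed in robot weeks and patients who stayed in standard weeks. That comparison is fair only if the two sets of weeks bring in similar patients.

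A fixed calendar opens two routes by which they may not. First, anyone who knows the order can foresee the arm when an elective admission is booked. Second, the arm is already set when patients are informed and decide whether to take part, so someone wary of technology has more reason to decline in a robot week than in a standard week. The selection that the Discussion describes for the sample as a whole would then act mainly in one arm. It would become a difference between arms rather than a limit on generalisability.

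**Working it through.** **1. The plan's own sample size.** Inputs from Participants and recruitment: f = 0.15, 2 groups, 2 measurements, alpha 0.05, power 0.80, stated N about 90. No pre-post correlation (rho) is given, so it is an assumption here. For the within-between interaction, lambda = f² × N × m / (1 − rho), with 1 and N − 2 degrees of freedom. With rho = 0.5: lambda = 0.0225 × 90 × 2 / 0.5 = 8.1 and power is 0.804; N = 88 gives 0.795. The stated 90 is therefore reproduced at rho = 0.5. Other values do not reproduce it: rho = 0 needs 178, 0.3 needs 126, 0.7 needs 56 and 0.8 needs 38.

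**2. The design effect on the change scale.** The between-arm difference in change is 4f = 0.60 outcome SDs. The SD of change is √(2 × (1 − rho)), which is 1 outcome SD at rho = 0.5, so the design effect is also 0.60 SD of change.

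**3. What the ANOVA removes.** With two time points, the interaction test is a comparison of mean change between arms. A stable baseline difference in level cancels. A difference in how much the two sets of patients would change without any robot does not cancel.

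**4. Illustration of size.** All inputs are assumed; none is in the document. Suppose 40% of eligible patients are technology-averse, their mean change is 0.5 SD lower even without a robot, and in robot weeks only they consent at one half or one quarter of the usual rate.

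- Half: averse share = 0.4 × 0.5 / (0.4 × 0.5 + 0.6) = 0.25. Bias = (0.40 − 0.25) × 0.5 = 0.075 SD.
- Quarter: averse share = 0.4 × 0.25 / (0.4 × 0.25 + 0.6) = 0.143. Bias = (0.40 − 0.143) × 0.5 = 0.129 SD.

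These are 0.075 / 0.60 = 12.5% and 0.129 / 0.60 = 21.5% of the design effect.

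**5. Effect on the test.** With no true effect and N = 90 split equally, a spurious difference b in change gives a noncentrality of b × √(90/4) on 88 degrees of freedom.

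| Spurious difference (SD of change) | False-positive rate |
|---|---|
| 0 | 5.0% |
| 0.075 | 6.4% |
| 0.10 | 7.6% |
| 0.129 | 9.3% |
| 0.20 | 15.5% |
| 0.30 | 29.1% |

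**6. What a random order would change.** If numbers of standard and robot weeks stay equal, power at N = 90 remains 0.804. An unrestricted coin toss per week would average 0.796 over 52 active weeks and 0.756 over 10 (equal patients per week assumed), so the order should be balanced. The chance of guessing the next week's arm is 100% under strict alternation, 75% with blocks of 2 weeks, about 71% with blocks of 4 and 50% with an unrestricted order.

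**7. Room for the staff pairs.** The article says "the study will be conducted over 2 years or less if the desired sample size is reached sooner". At full length that is about 104 weeks, hence about 52 active weeks. Three standard-then-robot pairs use 6 of them, leaving about 46 to randomise.

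**The case against.** The best defence starts from the text. All eligible patients are to be invited, so a reader who infers that staff will choose whom to approach by arm goes beyond the document. Information and consent are listed before allocation, and nothing says that the arms receive different information or that the arm is disclosed first. That recruiters know the arm is an inference from the fixed calendar, though a direct one. Steering of bookings is possible but not shown. The article spells out only weeks 1 to 5, and Figure 1 is not available, so continued alternation is also inferred. These points stand, but they do not remove the risk: the week has decided the arm before the consent form is presented.

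A second objection is that selective consent creates a spurious benefit only if technology-averse patients would improve less even without a robot. If aversion merely lowers their response to the robot, selection changes whose effect is estimated, which is close to the generalisability limit already conceded. This stands, and it is why 0.08 to 0.13 SD must not be read as an estimate of bias in this trial.

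Third, baseline measurement with a group-by-time test does protect against differences in level. That is correct; only differences in propensity to change remain.

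Fourth, a reader might infer that randomising week order would cure differential consent. It would not. Once a robot week begins, a 120 cm robot supervised by a researcher is on the ward, and those taking consent can see it. Random order protects booking; consent needs its own measure, and that can work only in part.

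Finally, the lack of randomisation is disclosed. That general concession does not mention selection that differs between arms, and it removes no bias from H3 or H4.

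**Conclusion.** The point holds as a design weakness that can be reduced cheaply. Allocation by a fixed calendar makes the arm predictable at booking and settled before consent, and the planned ANOVA does not protect H3 and H4 against arm-specific differences in who tends to change. The limitations section covers the sample as a whole but not this difference between arms.

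The document does not show that such bias will occur, and its size is unknown. The 0.08 to 0.13 SD figure, with false-positive rates of 6.4% to 9.3%, rests on an assumed averse share, an assumed difference in change without the robot and assumed consent ratios. Its comparison with 0.60 SD also needs a pre-post correlation of 0.5, which the article never states. The change is worth making because it costs little, not because a large bias has been demonstrated.

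**What to change.** 1. **Week order.** Randomise the order of study weeks in balanced blocks, preferably of varying size, from a computer-generated list held off the ward and released at the start of each week. Keep the three standard-then-robot staff pairs (start, one year, end) in fixed order. The last pair has no fixed date if recruitment finishes early, so the list must allow for it. This step protects booking.
2. **Consent and baseline.** Use one information sheet for both arms. Complete consent and baseline questionnaires before the patient is told the arm and, where possible, before any contact with the robot. This acts on differential consent, but only partly because the robot is visible.
3. **Reporting.** Report eligible, approached and consenting counts by arm, and add to the limitations that consent may differ between robot and standard weeks.

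Cost: a list, a short procedural text and three counts per arm. Supervision rosters get shorter notice, adjacent study weeks may share an arm, and concealment stays incomplete. N stays at 90 and power at 0.804 under the assumptions above. Patients are already grouped by week under the present plan, so the change adds no new clustering.
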